### Ethics Approval

The study was approved by the Datta Meghe Institute of Higher Education and Research Institutional Ethics Committee (approval number DMIHER [DU]/IEC/2024/169; approval date: January 31, 2024). All participants will be informed about the study and will provide written informed consent and assent before enrollment. All data on research participants will be kept strictly confidential. Patient information will be used only with the explicit permission of the individuals. There are no financial or conflicting interests to declare. The principal investigator will be responsible for preserving and maintaining all data collected during and after the study. The final trial dataset will be made available to the principal investigator upon formal request for research and publication purposes only, and access will be granted in a deidentified format.

In accordance with the policies of Ravi Nair Physiotherapy College and Datta Meghe Institute of Higher Education and Research, appropriate care will be provided to research participants if their involvement in the trial results in any harm. All information collected during or after the study will be used solely for academic and research purposes, with the ultimate aim of publication in a reputable journal. The key trial procedures, including enrollment, interventions, and assessments, are summarized in Table 1.

**Table 1 table1:** Demographics and clinical characteristics of the patients.

Confounders		Enrollment	Completed the treatment	Dropout (lost to follow-up/death)
**Age (years)**				
	14-21	✓	✓	✓
	22-30	✓	✓	✓
	31-38	✓	✓	✓
	39-46	✓	✓	✓
	47-55	✓	✓	✓
	56-64	✓	✓	✓
	65-70	✓	✓	✓
**Sex**				
	Male	✓	✓	✓
	Female	✓	✓	✓
**Cancer type**				
	Skin	✓	✓	✓
	Lungs	✓	✓	✓
	Female breast	✓	✓	✓
	Prostrate	✓	✓	✓
	Colon and rectum	✓	✓	✓
	Cervix and uterus	✓	✓	✓
	Head and neck	✓	✓	✓
**Chemotherapy type**				
	Cisplatin	✓	✓	✓
	Paclitaxel	✓	✓	✓
	5-Fluorouracil	✓	✓	✓
	Carboplatin	✓	✓	✓
	Dacarbazine	✓	✓	✓
	Temozolomide	✓	✓	✓
	Nab-paclitaxel	✓	✓	✓
	Oxaliplatin	✓	✓	✓

### Eligibility Criteria

#### Inclusion Criteria

Recently diagnosed patients with stage I to III cancers who are scheduled to receive a defined number of chemotherapy cycles involving platinum-based compounds.Patients currently undergoing chemotherapy treatment.Patients receiving taxane- or platinum-based compounds, including cisplatin, carboplatin, or oxaliplatin.Patients with grade I or II cognitive impairment as per the National Cancer Institute’s standard toxicity criteria.Patients scheduled to receive a minimum of 4 cycles of chemotherapy with any of the aforementioned platinum-based agents.Male and female patients aged between 14 and 70 years.Patients receiving chemotherapy drugs approved by the National Cancer Board.

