#### Exclusion Criteria

Patients with preexisting cognitive impairment.Patients with a history of traumatic brain injury.Patients with any prior psychological disorder that could affect cognitive function.Patients who have not received any chemotherapy cycles following cancer diagnosis or treatment.Patients with a previous history of cancer or prior exposure to chemotherapeutic drugs.Patients with neurological conditions affecting the brain or spinal cord, including vascular dementia, multiple sclerosis, amyotrophic lateral sclerosis, Alzheimer disease, Lewy body disease, stroke (cerebrovascular accident), or Huntington disease; as well as those taking medications known to impair cognition, such as benzodiazepines.Patients using cholinesterase inhibitors or antipsychotics; those with current or recent (within the past 6 months) alcohol or drug use disorders; those exhibiting behavioral changes such as depression, anxiety, or stress; and individuals with systemic conditions that may interfere with cognition, such as hypothyroidism, folic acid or vitamin B12 deficiency, or viral infections (eg, syphilis, HIV). Patients with visual or speech impairments (eg, aphasia) will also be excluded.

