### Selection of Participants

After obtaining ethical clearance from the Institutional Ethics Committee, patients diagnosed with cancer and scheduled to undergo chemotherapy will be identified at Siddharth Gupta Memorial Cancer Hospital. Permission will be sought from the treating residents, and eligible patients who meet the inclusion criteria will be enrolled after obtaining informed consent. Treatment will commence within 1 week of initiating the chemotherapeutic agent, and baseline data will be recorded. Participants will receive cognitive rehabilitation focusing on memory, attention, information processing, and executive function, with the aim of enhancing cognitive performance and improving quality of life. The first outcome measure, the Mini-Mental State Examination (MMSE), will be administered before the initiation of chemotherapy along with baseline data to assess cognitive function. Subsequently, the Montreal Cognitive Assessment will be conducted over 4 chemotherapy cycles. Participants will undergo the intervention 5 days per week, and following the completion of the 4 chemotherapy cycles, postintervention baseline data will be recorded. The outcome measures will be used to assess the degree of cognitive impairment. Follow-up assessments will be conducted after each chemotherapy cycle and weekly after completion of the intervention. Baseline outcome measures will be recorded after 4 chemotherapy cycles, and follow-up evaluations will be carried out once a week for 4 consecutive weeks.

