## Discussion

### Anticipated Findings

This study will evaluate and compare the effects of cognitive rehabilitation and conventional therapy on cognition in patients with CICI. It is anticipated that this framework will significantly enhance the cognitive functions of patients receiving cognitive therapy as an intervention alongside conventional management protocols.

We hypothesize that cognitive training will result in measurable changes in brain magnetic resonance imaging, including improved perfusion, enhanced white matter connectivity (particularly involving the hippocampus), and increased brain volume (including the hippocampus). We have designed a randomized controlled trial (RCT) to investigate the effects of cognitive training and physical exercise on cognitive functioning in patients with cancer who have undergone chemotherapy and reported cognitive difficulties confirmed by standardized and validated neuropsychological assessments. Several underlying mechanisms may explain the effectiveness of the therapies included in this study. Cognitive rehabilitation and active exercises (such as weight training, aerobic training, dance, and yoga) may enhance physical capacity by counteracting reduced activity levels during or after cancer treatment [23]. Furthermore, increased physical activity can positively influence mental health. Psychosocial therapies promote activity management and stress coping, thereby reducing fatigue. Cognitive rehabilitation enhances neuroplasticity, enabling the brain to reorganize and adapt in response to injury, and helps develop compensatory strategies that allow individuals to manage cognitive deficits more effectively. It also contributes to building cognitive reserve, thereby reducing the risk of cognitive decline and promoting resilience. Several RCTs have demonstrated the efficacy of cognitive rehabilitation in improving cognitive function and quality of life, as well as in reducing symptoms of anxiety and depression in individuals with CICI [24]. Meta-analyses have further shown that cognitive rehabilitation is associated with significant improvements in cognitive function, particularly in attention and memory [25].

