### Future Direction

The data on the prevalence rates of cognitive impairment in cancer survivors after chemotherapy accounted for variables such as age and time since therapy termination. Subgroup analyses and meta-regression were used to examine potential influences on prevalence estimates. The criteria for performing meta-regression were derived from Cochrane Guidance 35 [38]. A comprehensive meta-analysis was used to conduct the meta-regression. This review represents the first systematic comparison of prevalence rates of cognitive impairment in women with BC that has considered all methods used to ascertain impairment and evaluate long-term prevalence. Mean prevalence rates for CICI across all time points were 44% based on self-reports and 6% based on short cognitive screening [39]. The cognitive training intervention appears effective and may help reduce the deterioration of cognitive function in patients with CICIs.

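### Enrolment and baseline are timed before chemotherapy-induced impairment can exist, which contradicts the grade I or II entry criterion, two exclusions and the stated target population

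*Protocol article*

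**What the plan says.** **Who the trial is for.** The Abstract (Methods) says that the 60 people randomised have cognitive impairment caused by chemotherapy. The Objectives are to improve cognition and quality of life in patients with CICI.

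**Inclusion Criteria.** Entry requires "Patients with grade I or II cognitive impairment", graded on the NCI toxicity scale. It also requires "Patients currently undergoing chemotherapy treatment", although another criterion describes recently diagnosed patients whose cycles are still scheduled. On drugs, two criteria refer to platinum-based agents and a third admits taxanes or platinum.

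**Exclusion Criteria.** Three exclusions bear on timing: "Patients with preexisting cognitive impairment"; patients who have had no chemotherapy cycle; and "Patients with a previous history of cancer or prior exposure to chemotherapeutic drugs".

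**Selection of Participants.** Patients are identified when chemotherapy is planned, and those who meet the inclusion criteria are enrolled after consent. The MMSE, a primary outcome, is given with the baseline data before chemotherapy begins. On the start of the programme the section states: "Treatment will commence within 1 week of initiating the chemotherapeutic agent, and baseline data will be recorded". The same section later uses the word baseline for measurements taken after four cycles.

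**Anticipated Findings.** The Discussion describes "patients with cancer who have undergone chemotherapy and reported cognitive difficulties confirmed by standardized and validated neuropsychological assessments".

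**The concern.** The criteria describe a treatment trial in patients who already have a deficit. The enrolment procedure describes patients at the threshold of chemotherapy, who cannot yet have that deficit. These are different questions. In the first, success is recovery from an impaired starting point; in the second, it is less decline from an intact one.

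What is at stake is the meaning of the result. If the procedure is followed, a difference between arms would be reported as improved cognition in CICI although the baseline came before any chemotherapy. The pre-to-post tests within each group, planned in the Abstract, would measure net change across the start of chemotherapy and not recovery from impairment.

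**Working it through.** The point is one of logic and timing, so the main check sets the sections against each other.

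**1. The sample size is not in dispute.** With the plan's inputs (d = 0.8, z-values 1.96 and 0.84, ratio 1):

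n = 2 × (1.96 + 0.84)² / 0.8² + 1.96² / 4 = 24.5 + 0.96 = 25.46, rounded up to 26 per group.

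The plan's allowance for 15% dropout gives 26 × 1.15 = 29.9, hence 30 per group and 60 in total. The figure reproduces. The 0.8 is labelled as estimated and belongs to the trial as framed, that is, improvement in CICI.

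**2. The criteria on their own.** Take *preexisting* to mean before chemotherapy, and *prior exposure* to mean treatment for an earlier cancer. The inclusion and exclusion lists then fit together: a patient in a first course, with at least one cycle given and new grade I or II impairment.

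**3. That patient on the Selection of Participants timeline.** At the pre-chemotherapy MMSE there are two cases:
- *Impaired.* The impairment came before chemotherapy, so it is not chemotherapy-induced and falls under the exclusion of preexisting impairment.
- *Not impaired.* The grade I or II criterion is not met.

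In both cases the patient has had no cycle and meets that exclusion too. Nobody satisfies all the rules at that time point.

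**4. The most favourable variant.** Suppose eligibility is judged just before the programme starts, up to one week after the first agent. New impairment would have to arise and be graded inside that week. The baseline MMSE would still predate it, so it would not describe the impaired state that the trial sets out to improve.

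**5. Consequence for the MMSE.** The Outcome Measures section gives a maximum of 30 and treats 24 or above as normal. A participant in the normal range at baseline can gain at most 30 − 24 = 6 points, and none if already at 30. Little upward change can be observed on this outcome in participants without a deficit.

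**6. Drug class.** Read together, the inclusion criteria do not settle whether a patient receiving a taxane without platinum is eligible.

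**The case against.** The strongest reply is that the criteria govern. They are coherent on an ordinary reading (step 2), and Selection of Participants itself enrols only patients who meet them. Identifying patients early need not mean enrolling them unimpaired. The Discussion sentence about patients who have completed chemotherapy is loose text and sets no enrolment rule.

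Much of this stands. The inclusion and exclusion lists need not conflict with each other, and it would be wrong to say that the criteria alone leave almost nobody eligible. The reply does not rescue the timing: the section that applies the criteria also fixes the MMSE before chemotherapy and the programme start within a week of the first agent, and steps 3 and 4 show that these cannot be combined with impairment arising from chemotherapy.

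A reader might go further and infer that most participants will be unimpaired and that power collapses accordingly. The protocol does not support that:
- The grade criterion applies at enrolment, so a mostly unimpaired sample is an inference about conduct and is not stated.
- The prevalences in the article do not fit the purpose. One sentence reads "Mean prevalence rates for CICI across all time points were 44% based on self-reports and 6% based on short cognitive screening" and comes from a review in women with breast cancer; the figure of up to 75% in the Background refers to the period after chemotherapy. None describes mixed cancers at the start of treatment.
- A dilution calculation would also need zero effect in unimpaired participants. Nothing in the article supports this, and such participants could benefit through less decline.

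A reader might also cite Table 1, which lists drugs that are neither platinum nor taxane. That table is a template for patient characteristics, not an eligibility list, and other agents may be given in combination.

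**Conclusion.** The concern holds as an internal contradiction. The timing in Selection of Participants is incompatible with the grade I or II criterion, with the exclusions of preexisting impairment and of patients without a cycle, and with the target population in the Abstract and Objectives. If that timing is followed, the trial compares prevention of decline under an objective of improving cognition in CICI.

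This rests on one assumption: that the baseline MMSE and programme start happen when that section says they do. The size of the effect on the sample or on power cannot be given, because the protocol does not state how many participants are impaired at enrolment. The unresolved drug-class wording is a separate, smaller point.

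**What to change.** Reconcile the Inclusion Criteria, Exclusion Criteria and Selection of Participants to one population and one baseline time point. Two coherent versions are open to the sponsor:

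- **Treatment question.** Randomisation and baseline follow documented grade I or II impairment that arose in the current course. *Preexisting* and *prior exposure* are defined as before that course. This matches the objectives as written.
- **Prevention question.** Enrolment stays at the start of chemotherapy, the grade criterion is dropped, the objectives and conclusion are restated as prevention, and d = 0.8 is justified again for that contrast.

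The start of the programme relative to chemotherapy must be made consistent with whichever is chosen. The platinum-only and taxane-or-platinum wording must also be reconciled; the sponsor must decide which applies.

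The Results section reports 60 participants enrolled by November 9, 2024 (the Abstract puts this in the future tense), and rewording cannot change who they are. For each participant, record the NCI grade and the number of cycles received, both at randomisation and at the baseline MMSE, and limit the conclusion to the population these records show.

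The cost is a protocol amendment, two data fields and possibly a narrower conclusion. Whether more participants would be needed cannot be judged until those records are available.

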#### Exclusion Criteria

Patients with preexisting cognitive impairment.Patients with a history of traumatic brain injury.Patients with any prior psychological disorder that could affect cognitive function.Patients who have not received any chemotherapy cycles following cancer diagnosis or treatment.Patients with a previous history of cancer or prior exposure to chemotherapeutic drugs.Patients with neurological conditions affecting the brain or spinal cord, including vascular dementia, multiple sclerosis, amyotrophic lateral sclerosis, Alzheimer disease, Lewy body disease, stroke (cerebrovascular accident), or Huntington disease; as well as those taking medications known to impair cognition, such as benzodiazepines.Patients using cholinesterase inhibitors or antipsychotics; those with current or recent (within the past 6 months) alcohol or drug use disorders; those exhibiting behavioral changes such as depression, anxiety, or stress; and individuals with systemic conditions that may interfere with cognition, such as hypothyroidism, folic acid or vitamin B12 deficiency, or viral infections (eg, syphilis, HIV). Patients with visual or speech impairments (eg, aphasia) will also be excluded.

### Selection of Participants

After obtaining ethical clearance from the Institutional Ethics Committee, patients diagnosed with cancer and scheduled to undergo chemotherapy will be identified at Siddharth Gupta Memorial Cancer Hospital. Permission will be sought from the treating residents, and eligible patients who meet the inclusion criteria will be enrolled after obtaining informed consent. Treatment will commence within 1 week of initiating the chemotherapeutic agent, and baseline data will be recorded. Participants will receive cognitive rehabilitation focusing on memory, attention, information processing, and executive function, with the aim of enhancing cognitive performance and improving quality of life. The first outcome measure, the Mini-Mental State Examination (MMSE), will be administered before the initiation of chemotherapy along with baseline data to assess cognitive function. Subsequently, the Montreal Cognitive Assessment will be conducted over 4 chemotherapy cycles. Participants will undergo the intervention 5 days per week, and following the completion of the 4 chemotherapy cycles, postintervention baseline data will be recorded. The outcome measures will be used to assess the degree of cognitive impairment. Follow-up assessments will be conducted after each chemotherapy cycle and weekly after completion of the intervention. Baseline outcome measures will be recorded after 4 chemotherapy cycles, and follow-up evaluations will be carried out once a week for 4 consecutive weeks.

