## Methods

### Trial Design

This is an equal allocation, parallel-group, 2-arm superiority study, with the sample size distributed equally between the 2 groups. Patients will be evaluated according to predetermined inclusion and exclusion criteria and will be recruited from Siddharth Gupta Memorial Cancer Hospital in Sawangi, which is affiliated with Acharya Vinoba Bhave Rural Hospital. After obtaining informed consent, eligible participants will be selected through simple random sampling using computer-generated random numbers. All patients will be informed about the study procedures and asked to provide written consent before participation. The trial will include patients with a medical diagnosis of cancer who are currently undergoing chemotherapy. Sequence generation will be performed using computer-generated random numbers.

The allocation concealment mechanism will involve simple random sampling. Study participants will be randomly assigned using computer-generated random numbers. Randomization will be conducted by a researcher not involved in participant recruitment. To ensure allocation concealment, opaque sealed envelopes will be used, which will be opened only after participants are deemed eligible for treatment by the research team. Data collection will be carried out after participants are assigned to their respective intervention groups, with outcomes assessed and recorded during the preintervention phase. Postintervention data collection will be conducted after 4 weeks of intervention.

In data management, information obtained will be summarized using frequency and percentage for qualitative data, and mean and SD for quantitative data. Figure 1 presents the CONSORT (Consolidated Standards of Reporting Trials) flow diagram outlining the study design. See Multimedia Appendix 1 for the SPIRIT (Standard Protocol Items: Recommendations for Interventional Trials) checklist.

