### Participant Timeline

Pre- and postbaseline data will be collected, followed by a 4-week intervention period. After the completion of the 4 weeks, postintervention outcomes will be assessed. The study design is illustrated in the CONSORT flowchart presented in Figure 1.

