### Statistical Analysis

For demographic factors, all data will be summarized using baseline characteristics, expressed as the mean and SD for continuous data and as frequency and percentage for categorical data.

The analysis of outcome variables will primarily focus on continuous variables. For parametric data, the minimum, maximum, mean, SD, SE, and 95% CI will be summarized. The normality of continuous outcome variables will first be tested using the Kolmogorov-Smirnov test at a 5% level of significance (*P*≤.05). If the data are found to deviate from normality, a nonparametric test will be applied to determine significance. An independent *t* test will be conducted for group comparisons to assess significant differences at the 5% level (*P*≤.05). The intervention groups will receive (1) cognitive training supplementing traditional physical treatment and (2) traditional physical treatment.

The effect size at different assessment visits between the 2 groups will be calculated for the variables MMSE and Montreal Cognitive Assessment. For nonnormal data, descriptive statistics will include the mean, median, and lower and upper quartiles. The Mann-Whitney test will be applied to determine statistical significance when nonparametric methods are required.

Categorical variables will be summarized using frequency (n) and percentage. Chi-square analysis will be performed to evaluate efficacy across categorical variables. An intention-to-treat analysis will be applied to minimize attrition bias among participants, including those lost to follow-up or deceased due to adverse effects of chemotherapeutic drugs.

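### One section ties the post-intervention recording to finishing 4 chemotherapy cycles while two others place it after 4 weeks of intervention, so patients who stop chemotherapy early can miss it

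*Protocol article*

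**What the plan says.** Three sections of the protocol article set the time of the post-intervention assessment.

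- **Selection of Participants** uses completion of chemotherapy: "following the completion of the 4 chemotherapy cycles, postintervention baseline data will be recorded". Its closing sentence repeats the 4-cycle anchor and adds that "follow-up evaluations will be carried out once a week for 4 consecutive weeks".
- **Trial Design** uses time on the programme: "Postintervention data collection will be conducted after 4 weeks of intervention".
- **Participant Timeline** agrees with Trial Design: "After the completion of the 4 weeks, postintervention outcomes will be assessed".

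Selection of Participants also schedules interim measurement. It says that "the Montreal Cognitive Assessment will be conducted over 4 chemotherapy cycles", and that "Follow-up assessments will be conducted after each chemotherapy cycle and weekly after completion of the intervention".

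Statistical Analysis gives the analysis principle: "An intention-to-treat analysis will be applied to minimize attrition bias among participants, including those lost to follow-up or deceased". Eligibility requires only that at least 4 cycles be scheduled, not that they be completed.

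**The concern.** Completing 4 cycles happens after randomisation and depends on how chemotherapy goes. Some patients will never reach it, and others will reach it at different times. Used as the trigger for the post-intervention recording, it has two effects.

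- A living, attending patient whose chemotherapy ends early has no such recording and does not enter the weekly series that follows it.
- Patients whose cycles are delayed are measured later than the rest, so the final measurement is not taken at a common time since randomisation.

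An intention-to-treat comparison needs outcomes from all randomised patients, including these. An analysis plan can say how missing values are handled, but it cannot recover a visit that the protocol did not schedule. The other two sections use a different anchor, so a reader cannot tell which rule governs.

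**Working it through.** **1. The timing rules side by side**

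| Section | Trigger | Patient who stops after cycle 2 | Patient with delayed cycles |
|---|---|---|---|
| Selection of Participants, final recording and the 4 weekly follow-ups after it | 4 cycles completed | not reached | reached late |
| Selection of Participants, interim assessments | each cycle | available after cycles 1 and 2 | available, shifted in time |
| Trial Design; Participant Timeline | 4 weeks of intervention | available, if read as calendar time | available on time |

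The weekly follow-ups are themselves anchored in two ways within Selection of Participants: once to the end of the intervention and once to the 4 cycles. No section withdraws a patient who stops chemotherapy. Equally, none says that a patient who stops the programme is still assessed.

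**2. The plan's own sample size** (inputs from Sample Size: d = 0.8, z = 1.96 and 0.84, allocation ratio 1)

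n = 2 × (1.96 + 0.84)² / 0.8² + 1.96² / 4 = 24.5 + 0.96 = 25.46, rounded up to 26 per group. Adding 4 for dropout gives 30. The stated figure reproduces. At the planned 15% loss, 30 × 0.85 = 25.5 per group remain.

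**3. Size of the loss if the cycle trigger alone governed**

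Assumption: 10% to 30% of patients stop before 4 cycles, equally in both arms, and there is no other dropout. The document gives no rate. The number with the final recording is n = 30 × (1 − loss). Power is that of a two-sided 5% two-sample t test with 2n − 2 degrees of freedom and noncentrality 0.8 × √(n/2).

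| Loss | n per arm | Power |
|---|---|---|
| 10% | 27 | 0.822 |
| 15% | 25.5 | 0.800 |
| 20% | 24 | 0.774 |
| 25% | 22.5 | 0.746 |
| 30% | 21 | 0.716 |

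**4. Bias under the same condition**

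Let p1 and p0 be the proportions stopping in each arm, and D the gap in SD units between completers and stoppers, taken as the same in both arms. The completer mean in an arm equals the overall mean plus p × D, so the arm difference shifts by (p1 − p0) × D. With an assumed 10% versus 20% stopping, the absolute shift is 0.10 × 0.5 = 0.05 SD for D = 0.5, and 0.10 × 1.0 = 0.10 SD for D = 1.0. With equal stopping it is zero.

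**The case against.** A reader might infer that outcome data are collected only after 4 completed cycles, that early stoppers never reach an outcome visit, and that the intention-to-treat statement is therefore contradicted. The document does not support this. Trial Design and Participant Timeline both state an assessment after 4 weeks that does not depend on chemotherapy. Selection of Participants itself adds assessments after each cycle, including the Montreal Cognitive Assessment, which is listed as a primary outcome. The intention-to-treat sentence keeps patients who are lost or have died, and nothing removes patients who stop chemotherapy. Missing-data handling may properly sit in an analysis plan that is not shown.

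It is also fair to say that the harm is conditional. If the 4-week rule governs, most of it disappears. The stopping rates are assumed, the sample size already allows for 15% dropout, and nothing in the document suggests that stopping would differ between arms.

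All of that stands and limits the point. It does not remove it. The cycle trigger is stated twice in the section with the most detailed visit schedule, and it conflicts with the other two. Per-cycle assessments end when the cycles end, so they do not replace the final recording. The only instrument named for the cycle period is the Montreal Cognitive Assessment, while the abstract plans group comparisons before and after treatment. Simply harmonising the wording could settle on the cycle trigger and leave the problem in place.

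**Conclusion.** The point holds as an inconsistent and partly completion-dependent assessment schedule. It does not hold as a total loss of outcomes in early stoppers or as a contradiction of intention-to-treat.

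The size cannot be fixed from the document. The power range of about 82% to 72% is an upper illustration: it assumes that the cycle trigger alone governs and that every early stopper lacks the final recording. At 10% loss the trial would still have more than its required 26 per arm. At 15% the whole dropout allowance is used, and any further loss takes power below 80%. The illustrated bias of 0.05 to 0.10 SD is modest against a design effect of 0.8. It rests on unequal stopping and on the same completer gap in both arms. The change should be made because it is cheap and removes an avoidable source of missing and mistimed data.

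**What to change.** Reconcile Trial Design, Selection of Participants and Participant Timeline on one rule:

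- Replace the cycle-completion trigger with one post-intervention assessment at a fixed number of weeks from randomisation, in a stated window, for every randomised patient. Time the weekly follow-ups from that same visit.
- Carry out these assessments whether or not chemotherapy or the trial programme was shortened, delayed or stopped, unless the patient withdraws consent for assessments.
- Record the date and reason of any discontinuation of chemotherapy or of the programme.
- State that these visits supply the data for the intention-to-treat analysis.

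This concerns only when outcomes are measured and leaves treatment untouched. The cost is an amendment to the wording, with no new instruments and no extra patients. There are two downsides: some visits will fall outside a chemotherapy attendance, and the estimated effect may be slightly smaller because patients who did not complete are included.
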